### Intervention

The intervention group received a structured exercise rehabilitation program, which was mainly developed by our team through preliminary literature research and by inviting experts in the relevant fields (including hematologists, nurses, and rehabilitation therapists) [24]. The exercise rehabilitation was divided into 3 phases according to the different periods of the patient’s transplantation; each phase involved warm-up, formal, and finishing exercises, and was tailored according to the strength of each participant.Phase 1: Exercise rehabilitation in the transplantation module (neutrophil and platelet engraftment to out of the transplantation module). Considering that the patient was weak in the early post-transplantation period, exercises in this phase were mainly bed and bedside activities. The warm-up exercises were mainly lip reduction-abdominal breathing with progressive relaxation exercises (involving hand muscles, arm muscles, hip muscles, thigh muscles, calf muscles, and toe muscles), for exercising the muscles of the whole body; the aerobic exercises in formal exercises were mostly performed with bed-side bicycles; the resistance exercises were mainly bed or bedside elastic band exercises performed by the patient (involving biceps, triceps, psoas major, abdominal, gluteal and foot muscles); and the finishing exercises wrapped up with progressive relaxation exercises.Phase 2: Exercise rehabilitation in the hematology ward (during admission to the general ward).

Patients who were transferred from the transplant module were in better condition than before, so it was appropriate to increase the intensity of exercises and move from bed to floor. The warm-up exercise included 6 movements (including head exercise, shoulder circuit, chest expansion, waist circuit, knee circuit, and wrist and ankle exercises) to avoid injury during exercise; the aerobic exercise options for formal exercises included Baduan Jin and Tai Chi; the resistance exercise was a stretch band exercise consisting of 8 movements (more difficult than before); and the finishing exercise was a relaxing stretch of the whole body in 8 movements from head to toe.Phase 3: Out-of-hospital exercise rehabilitation (post-discharge to 100 days post-transplantation).

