The patient continued the exercise pattern of phase 2. Meanwhile, after taking into account the patients’ return to society, exercise modalities such as cycling, jogging, brisk walking and stair climbing were added to the aerobic exercises. In addition to stretch band exercises, patients were recommended a suitable form of exercise based on the definition of 3 to 6 metabolic equivalents (MET) for moderate-intensity exercises released by the United States Department of Health and Human Services (HHS) [25].

Videos prepared by researchers were used to teach exercises of all movements. Patients could broadcast the videos on TV or mobile phones. As recommended by the experts, the warm-up exercises and finishing exercise should last for 5–10 min each time. Aerobic exercises were performed twice a week for 20–25 min. Resistance exercises were implemented thrice a week for 15–20 min, and the appropriate Thera-band elastic band was selected according to the patient’s platelet count [26]: (1) PLT < 20 × 10^9^/L: resistance exercise was not recommended; (2) 20 × 10^9^/L ≤ PLT < 30 × 10^9^/L: yellow elastic band (3.0 lbs); (3) 30 × 10^9^/ L ≤ PLT < 50 × 10^9^/L: yellow or red elastic band (3.7 lbs); (4) 50 × 10^9^/L ≤ PLT < 150 × 10^9^/L: red elastic band (3.7 lbs); and (5) PLT ≥ 150 × 10^9^/L: red or green elastic band (4.7 lbs) was recommended.

The exercise intensity was monitored using the target heart rate (THR) combined with the Rating of Perceived Exertion (RPE) Scale. To be specific, exercise intensity was targeted between 50 and 75% of heart rate (HR) reserve, in which THR = [(max HR − resting HR) × % intensity] + resting HR, where max HR = 220-age (for female) or 205-age (for male). Participants also used the RPE scale score of 12 ~ 14 points as the target exercise intensity. They followed the principle of gradual progression in the process of exercises.

Participants in the control group were randomized to usual care receiving usual care treatment according to the Chinese Expert Consensus on the Diagnosis and Treatment of Aplastic Anemia [27], including pre-HSCT workup, conditioning regimen, management of early issues, and late complications post-HSCT. In addition, access to educational materials on allogeneic bone marrow transplant was published by UpToDate [28]. Receiving health education and encouragement related to exercise, but there is no standardized program or specific requirements.

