### Variables and measurement instruments

Sociodemographic and clinical variables: To characterize the samples, sociodemographic and clinical data were extracted from the participants, containing age, gender, marital status, educational level, professional/employment status, household income, duration of AA, medication, and type of treatment.QoL: it was measured using the validated European Organization for Research and Treatment of Cancer Quality of Life Questionnaire-Core 30 (EORTC QLQ-C30) [29]. This questionnaire consists of 30 items covering 15 domains, which reflect the patient’s physical, role, emotional, cognitive and social functioning, a global quality of life domain, together with fatigue, nausea and vomiting, pain, dyspnea, insomnia, loss of appetite, constipation, diarrhea, and financial difficulties. All items were rated on a 4-point response scale ranging from 1 (not at all) to 4 (very much) points, except for the two items measuring general health and QoL (summarized as global QoL) that were rated on a visual analogue scale from 1 ~ 7 points. All scales were transformed to a percentile scale from 0 ~ 100 points, with the higher scores representing better functioning and global QoL, whereas the higher scores on the symptom scales indicated the higher levels of symptoms or problems.Upper limb muscle strength: it was assessed by measuring the grip strength using a hand dynamometer (EH101, Camry, China) [30]. To be specific, the participant was asked to sit upright in a chair and place the feet on the floor. The shoulder of the limb to be tested was kept adducted and neutral for rotation, with the elbow being flexed at 90°, wrist extension between 0 and 30° and ulnar deviation of 0 ~ 15°. The left and right hands were alternately measured thrice each and the average value was taken as the grip strength of the participant. During the test, the participants were constantly verbally encouraged to use their maximum strength.Lower limb muscle strength: it was evaluated with the Five Times Sit to Stand Test (FTSST) [31]. In brief, participants were required to sit in an armless chair at a standard height (45 cm) and tested on the duration of 5 sit-to-stand movements. In the test procedure, the participants were asked to stand upright with their upper body, with arms crossing over the chest and feet flat on the floor. Participants were asked to stand up completely without using their upper limbs and then sit down again.Fatigue: it was measured with the Brief Fatigue Inventory (BFI) questionnaire [32]. The BFI questionnaire covers 10 items. The first item determines whether there has been abnormal fatigue over the last week using a “yes” or “no” option. The other items determine the current level of fatigue and the impacts of fatigue on general activity, mood, walking ability, relationships with others, and enjoyment of life. Each item is based on a 0–10-point scale, with a score of 0 representing the best state and no fatigue, whereas that of 10 indicating the worst state of fatigue. Participants were asked to mark their answers to each question based on their perceived level of fatigue, and the overall fatigue level was measured by calculating the total score of items 2 to 10 divided by 9. To be specific, a score of 0 meant no fatigue, while those of 0.1 ~ 3.9, 4 ~ 6.9, 7 ~ 9.9, and 10 were indicative of mild, moderate, severe, and very severe fatigue, separately.Hematological indicators: These indicators included platelet (PLT), neutrophil (Neu), hemoglobin (HB), and reticulocyte (Ret) counts in the peripheral blood of participants.Exercise adherence: it was assessed by the exercise attainment rate, which was the number of people attaining the standard/total number of people × 100%. Exercise attainment was defined as exercising at least thrice a week for 30 min or longer (or ≥ 10 min each time for a cumulative total of 30 min).Adverse events: the proportion of adverse events occurring during the study period was determined.

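### The exercise-adherence outcome is a general activity threshold that does not match the prescribed programme of two aerobic and three resistance sessions a week

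*Protocol article*

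**What the plan says.** The Intervention section of the protocol article sets the weekly programme. "Aerobic exercises were performed twice a week for 20–25 min". "Resistance exercises were implemented thrice a week for 15–20 min". It adds that "the warm-up exercises and finishing exercise should last for 5–10 min each time", and describes the programme as one in which "each phase involved warm-up, formal, and finishing exercises". The elastic band is chosen by platelet count; at PLT below 20 × 10^9/L, "resistance exercise was not recommended". In phase 3, after hospital discharge, "exercise modalities such as cycling, jogging, brisk walking and stair climbing were added to the aerobic exercises", with no separate frequency or duration for the additions. For controls, "there is no standardized program or specific requirements".

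Exercise adherence is a named secondary outcome (Primary and secondary outcomes). Variables and measurement instruments defines it as the percentage of people who attain a standard: "Exercise attainment was defined as exercising at least thrice a week for 30 min or longer". A bracket then allows bouts of at least 10 min that add up to 30 min. The definition does not mention exercise type, the aerobic and resistance components, or platelet count. It does not say whether the 30 min accumulates per day or per week, or whether warm-up and finishing count.

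The Adherence section describes a daily log of exercise type and duration, with a reason required when no exercise was done. The Statistical analysis section describes adherence by frequencies and percentages only.

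**The concern.** An adherence outcome should show how much of the assigned programme was delivered. This one applies a different yardstick. A patient can meet it after leaving out a whole component, and a patient who follows the prescription can miss it. The programme has two components, and the second study hypothesis concerns muscle strength. A reader who wants to interpret a null result, particularly on strength, needs to know whether the resistance part, the aerobic part or both were done. A single pass rate on a general threshold cannot show that.

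**Working it through.** The plan states no figure for adherence, so there is none to reproduce. The check sets the prescribed week against the standard.

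**Inputs (Intervention section).** Aerobic: 2 per week, 20–25 min. Resistance: 3 per week, 15–20 min. Warm-up and finishing: 5–10 min each. Standard: at least 3 occasions a week of at least 30 min.

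**1. Warm-up and finishing counted, five separate days**

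| Durations | Aerobic session (min) | Resistance session (min) | Full complier: qualifying days | Resistance only: qualifying days |
|---|---|---|---|---|
| Lower limits | 20+5+5 = 30 | 15+5+5 = 25 | 2 (not attaining) | 0 (not attaining) |
| Midpoints | 22.5+7.5+7.5 = 37.5 | 17.5+7.5+7.5 = 32.5 | 5 (attaining) | 3 (attaining) |
| Upper limits | 25+10+10 = 45 | 20+10+10 = 40 | 5 (attaining) | 3 (attaining) |

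Weekly minutes at the midpoints: full programme 2 × 37.5 + 3 × 32.5 = 172.5; resistance only 3 × 32.5 = 97.5, or 57%. At the upper limits: 2 × 45 + 3 × 40 = 210 against 120, again 57%. Both patients are scored as attaining.

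**2. How often a full complier fails on this reading.** Of the 6 × 6 × 6 = 216 whole-minute combinations for a resistance session, 35 total less than 30 min (16.2%). No aerobic combination does. Treating combinations as equally likely and sessions as independent, which are assumptions:
- five separate days: all three resistance sessions must fall short, (35/216)^3 = 0.4%;
- one aerobic session on a resistance day: (35/216)^2 = 2.6%;
- both aerobic sessions on resistance days: only the remaining resistance day can fall short, 35/216 = 16.2%.

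**3. Warm-up and finishing not counted, 30 min per day.** Sessions last 15–25 min, so a qualifying day needs at least two of them. Five sessions give at most two such days. In phases 1 and 2 a full complier cannot attain on any timetable. Nor can a resistance-only patient, so the two are again scored alike.

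**4. PLT below 20 all week, phases 1 and 2, 30 min per occasion.** Resistance is withheld, which leaves two aerobic sessions and so at most two qualifying occasions against three required. Warm-up and finishing alone on the three resistance days would add only 10–20 min each. The patient followed the prescription and is scored as not attaining. In phase 3 the added activities could lift the patient over the threshold.

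**5. 30 min as a weekly total.** If the bracket lets a weekly total replace the three occasions, the patient in step 4 attains with 60–90 min. The threshold then falls to 30 of 172.5 midpoint minutes (30/172.5 = 17%).

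**6. Upper bound over the programme.** From about day 14 to day 100: 86/7 = 12.3 weeks, so 2 × 12.3 = 24.6 aerobic and 3 × 12.3 = 36.9 resistance sessions, about 61 in all. Omitting all of the roughly 25 aerobic sessions leaves every week attaining only if all three resistance sessions reach 30 min in every week. Under the assumptions of step 2, one such week has probability (181/216)^3 = 58.8%, and 12 in a row 0.588^12, about 0.2%.

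**The case against.** The strongest reply is that the outcome is called an attainment rate, which is a minimum-dose threshold. Any binary threshold scores partial and full compliers alike, and a general threshold can be applied to controls, who have no prescribed sessions. That is a good reason to keep the rule as an activity measure. It does not turn the rule into a measure of programme adherence, which is the name the outcome carries.

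The bracketed clause matters, and the article leaves it open. Read per occasion, it changes nothing above. Read as a weekly total, it removes the platelet point, but only by making the standard much looser. The mismatch remains either way.

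That any type of exercise counts is inferred from silence. If exercising means programme exercise only, a resistance-only patient can still attain and the low-platelet complier still does not.

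Three stronger conclusions may tempt a reader, and the document does not support them:
- *Full compliers usually fail.* With warm-up and finishing counted, they fail only at short durations. Failure is certain only if those minutes are excluded and the 30 min is per day.
- *Some 25 of 61 sessions will be skipped unnoticed.* That is an upper bound needing long resistance sessions every week. The first two phases are supervised, the third has daily check-ins and weekly calls, and the log would show the omissions.
- *The platelet rule materially distorts the rate.* The programme starts at neutrophil and platelet engraftment, so a whole week below 20 may be uncommon. The article gives no frequency.

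Component tables are commonly left to an analysis plan, and their absence alone would be no finding. Here, however, the article itself fixes the definition, and that definition does not fit the prescription.

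**Conclusion.** The point stands as a minor one. That the standard does not match the programme follows directly from the text. Its consequences depend on how the 30 min is counted:
- warm-up and finishing counted: omitting all aerobic work, 43% of midpoint minutes (100% − 57%), can go unseen;
- not counted, 30 min per day: full compliance with the stated schedule cannot attain in phases 1 and 2;
- 30 min per occasion: following the platelet rule for a whole week in phases 1 and 2 is scored as not attaining, with unknown frequency;
- weekly total: the platelet problem goes, but about 30 min a week passes as adherence.

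No reading makes the rate a measure of adherence to the prescribed sessions. The damage is confined to one descriptive secondary percentage. A reader might infer harm to the main result, but no other rule in the article uses the rate, and neither the quality-of-life analysis nor the sample size depends on it.

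**What to change.** In the intervention group, define exercise adherence from the existing log as sessions completed divided by sessions prescribed. Report it for aerobic and resistance separately and combined, and by phase (T0–T1, T1–T2, T2–T3). Remove resistance sessions withheld under the platelet rule from the denominator.

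Keep the present standard under a name such as general activity attainment. State whether the 30 min is per day or per week, and whether warm-up and finishing count. The exercise schedule does not change.

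The cost is a change of wording and a little more log processing, since type, duration and reasons for no exercise are already recorded. The downside is that the programme-adherence measure exists in one arm only. The article does not say whether controls keep the log; if they do not, using the general measure in both arms needs a short activity question for them.

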
### Participant timeline

The participant timeline is shown in Table 1.

**Table 1 Tab1:** Participant timeline

	STUDY PERIOD			
	Baseline	Post-allocation		
TIMEPOINT^a^	*t*_*0*_	*t*_*1*_	*t*_*2*_	*t*_*3*_
ENROLMENT:				
Eligibility screen	X			
Informed consent	X			
*Demographics*	X			
*Medical history*	X			
INTERVENTION:				
*[Intervention group]*		X	X	X
*[Control group]*		X	X	X
ASSESSMENTS:				
*[EORTC QLQ-C30]*		X	X	X
*[hand dynamometer]*		X	X	X
*[ FTSST]*		X	X	X
*[BFI]*		X	X	X
*[Number and volume of RBC and PLT transfusions]*				X
*[Hematological indicators]*		X	X	X
*[Recruitment rate]*				X
*[Drop-out rate]*				X
*[Exercise adherence]*		X	X	X
* [Adverse events]*				X

^a^***t***_***0***_: the neutrophil and platelet engraftment (± 1day); ***t***_***1***_: discharge from the transplantation module (± 1 day); ***t***_***2***_: hospital discharge (± 1 day); ***t***_***3***_: 100 days post-transplantation (± 5 days)

### Randomization and blinding

Eligible participants will be randomly divided into two groups in a 1:1 ratio. Randomization will be conducted using an automated permuted block. The block size will not be disclosed to study staff who are enrolling patients or assigning interventions. The computer-generated randomization sequence will be kept by an independent researcher not involved in the exercise rehabilitation assessment and will be kept in a sealed envelope. Since the intervention in this study is exercise rehabilitation, the interventionists and participants will not be blinded. Participants will be informed of the intervention after completing all baseline assessments. Outcome assessors will be blinded, so unblinding will not occur. And participants will be told not to reveal the intervention they received while performing the outcome measure.

### Sample size

PASS software was employed to assess the sample size. The sample size calculations were based on previous research on physical activity for hematopoietic stem cell transplantation for QoL [33]. The study will be a parallel-group randomized controlled trial with the quality of life being the primary outcome in the study. Based on a previous study [3], the mean QoL in the control group was estimated to be 56.3 ± 17.6, and exercise rehabilitation increased the QoL in the intervention group by 12.3 relative to the control group. With an alpha risk of 0.05 (bilateral) and a beta risk of 0.20, the sample size of each group was calculated to be at least 33 people. Considering the existence of factors including shedding, the samples were expanded by 20% on the premise of guaranteeing the minimum sample size. The samples were expanded to 41 cases in each of the two groups, with a total of 82 cases.

## Data management

A unique identifier will be provided for each participant who meets the inclusion criteria. An Excel file will be stored by the researcher. All data collected/analyzed will be entered into the Excel database.

### Safety/harms

Any adverse events that occur will be monitored and recorded throughout the trial. Potential minor adverse events that can be expected may be fatigue, tachycardia, dizziness, or blurred vision, which can be minimized mainly through assessment and monitoring. Based on the patient’s adverse events, a professional will assess and decide whether further treatment is required. If adverse events are reported, they will be collected and categorized according to expectedness, seriousness, severity, and potential relevance to the study. This information will then be relayed to the study’s steering committee, and the ethics committee will be informed accordingly.

### Auditing

The primary researcher will be responsible for continuous monitoring of the study and will report and discuss progress at monthly team meetings. Given that this is a single-center trial with limited sample size and low-risk interventions, a data monitoring committee has not yet been established. In the event of any adverse events, we will promptly report to the ethics committee.

### Protocol amendments

Any modifications to the study protocol will require re-approval from the respective ethics committee and will be updated on ClinicalTrials.gov.

## Statistical analysis

SPSS26.0 was adopted for statistical analysis of data. Missing data were filled in using the Last observation carried forward (LOCF) and statistical analysis was conducted following the intention-to-treat (ITT) principle. Statistical tests were carried out with two-sided tests and *P* 0.05 was considered a statistically significant difference. Gender, education level, marital status, exercise adherence, and incidence of adverse events were described as frequencies and percentages. In the meantime, age, duration of AA, time to HSCT and QoL, muscle strength, fatigue, PLT, Neu, HB, and Ret counts were described as means and standard deviations if they conformed to normal distribution, or median if they conformed to non-normal distribution. The chi-square test or *t-*test was employed to compare differences between the intervention and control groups. Taking into account the potential variations in age, gender, and education level, analysis of variance (ANOVA) was conducted to assess the development of outcomes over time. Additionally, repeated measures analysis was used to analyze scores at baseline and follow-up scores of all measures.

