Currently, meta-analyses have confirmed the positive impact of exercise interventions on the physical and psychosocial functioning and quality of life of transplant patients [15, 16]. However, as evidenced by the diversity of interventions and mixed hematologic and cancer populations, most of the existing studies have methodological limitations [17]. A mixed sample including both malignant and non-malignant hematology disorders that received HSCT was selected for most studies. No subgroup analysis was performed to determine whether it was the same hematologic disease. The symptoms and treatment modalities of patients with different hematologic diseases show significant differences. For example, malignant hematologic diseases (like leukemia) have a high risk of recurrence after transplantation, and disease recurrence is the leading cause of death after transplantation [18, 19]. By contrast, benign hematologic diseases such as AA have a lower risk of recurrence after transplantation, and the leading cause of death after transplantation refers to complications including graft-versus-host disease (GVHD) [20]. These differences in clinical characteristics support the need for exercise rehabilitation intervention studies in the HSCT-AA population. Meanwhile, we believe that studies on exercise interventions for malignant hematological diseases [21], lymphoma [22], and MDS [23] are also underway. To our knowledge, there is limited published literature on exercise rehabilitation in HSCT-AA patients. It provides an opportunity to examine the effectiveness of exercise interventions in benign but severe hematologic diseases such as HSCT-AA. The study hypotheses are as follows: (1) compared to the control group, exercise rehabilitation will result in a greater improvement on QoL (primary hypothesis); (2) compared to the control group, exercise rehabilitation will result in a greater improvement in muscle strength; (3) compared to the control group, exercise rehabilitation will result in greater improvement on fatigue and hematological indicators.

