#### Adherence

In addition, an exercise rehabilitation log was issued to the participants during the exercise period. The exercise log, which was required to be recorded faithfully each day, covered several aspects including type and duration of exercises, subjective exercise responses (like the assessment of pain, fatigue, emotional state, and distress), and adverse events. When no exercise was performed, the reason should be provided. The first two phases of exercise rehabilitation were supervised by the interventionists, while the third phase of out-of-hospital exercise rehabilitation was supervised by daily WeChat exercise punch cards and weekly telephone contact. The exercise rehabilitation program was from the participant’s neutrophil and platelet engraftment after transplantation (approximately 14 days post-transplantation) to 100 days post-transplantation.

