### Primary and secondary outcomes

In this study, participants’ QoL was the primary outcomes, whereas participants’ muscle strength, fatigue, hematological indicators, exercise adherence, and adverse events were the secondary outcomes. All outcomes were measured at the time of neutrophil and platelet engraftment (± 1 day, T0), discharge from the transplantation module (± 1 day, T1), discharge from the hospital (± 1 day, T2), and 100 days post-transplantation (± 5 days, T3). Evaluations of T0 will be administered by the [name] enrolling the patient as part of the baseline assessment. Follow-up evaluations will be administered by [name], who are blinded to the patient’s group allocation. All assessors will be trained by the rehabilitation therapist on the steering committee before the start of the trial, and periodic meetings between the evaluators will be established fortnightly to promote internal transparency and consolidate data collection procedures. T0, T1, and T2 measurements will be performed in the inpatient of hematology, and T3 measurements will be performed in the inpatient or outpatient clinic of hematology, depending on the patient’s follow-up results.

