### Limitations

Several limitations should be noted in this work. Firstly, HSCT-AA patients may be frail due to treatment and disease, and the patient attrition may be high after follow-up for 100 days post-transplantation. We will consider other measures to remind patients to participate in the follow-up study. Secondly, the control group was mainly provided with usual care together with exercise-related health education, which may have underestimated the intervention effect. Nevertheless, we consider that it would be unethical to include control subjects without any intervention. Finally, the white paper report mentions that HSCT patients should receive multimodal interventions, including exercise, nutrition, and return to work [34]. However, this study did not include a nutritional assessment or dietary intervention, which is considered another limitation of this exercise-focused intervention.

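### LOCF is fixed as the only missing-data method for patients expected to recover, so the day-100 contrast is biased if benefit builds late or dropout differs by arm

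*Protocol article*

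**What the plan says.** All references are to the protocol article.

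- **Method.** Statistical analysis: "Missing data were filled in using the Last observation carried forward (LOCF) and statistical analysis was conducted following the intention-to-treat (ITT) principle". No alternative or sensitivity analysis is stated. The repeated-measures analysis in the same section is described without any exception to this filling-in.
- **Outcome and visits.** Primary and secondary outcomes: "participants’ QoL was the primary outcomes", with all outcomes measured at T0 (engraftment), T1 (leaving the transplantation module), T2 (hospital discharge) and T3 (day 100).
- **Timing of T0.** Adherence places engraftment at "approximately 14 days post-transplantation".
- **Expected course.** Intervention, on phase 1: "Considering that the patient was weak in the early post-transplantation period". On phase 2: "Patients who were transferred from the transplant module were in better condition than before".
- **Expected loss.** Sample size expands the groups by 20% for loss. Limitations says that "the patient attrition may be high after follow-up for 100 days post-transplantation".
- **Routes to unequal loss.** Participants are not blinded (Randomization and blinding). A clinician can exclude a participant after a study-related adverse reaction (Criteria for discontinuing or modifying allocated interventions).

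**The concern.** LOCF treats a patient lost after T0 as staying at the T0 score until day 100, a span of about 100 - 14 = 86 days. The protocol's own account of recovery makes that assumption implausible. The programme also runs to day 100 and is hypothesised to bring greater improvement, so part of any benefit may arise after a patient's last observed visit. LOCF removes that part.

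If one arm loses more patients, that arm also receives more early, low scores. The difference in dropout is then turned into a difference in QoL, in favour of whichever arm loses fewer patients. Exclusion for study-related reactions could fall more on the exercise arm, and unblinded participants may leave for reasons tied to their allocation.

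Filled-in scores also enter the analysis as if they had been observed, so the standard errors take no account of the missing data. At stake is the estimate for the primary outcome, at the last visit and the end of the intervention.

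**Working it through.** **1. The plan's own figure.** Inputs from Sample size: difference 12.3, SD 17.6, two-sided alpha 0.05, power 0.80.

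n per arm = 2 × [17.6 × (1.960 + 0.842) / 12.3]² = 32.14, rounded up to 33, as stated. Allowing for 20% loss, 33 / 0.8 = 41.25, against the stated 41. The figures reproduce to within rounding. With 20% loss, 41 × 0.8 = 32.8 patients per arm have an observed T3 score, which gives completers about 80% power.

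**2. Formula for the LOCF contrast.** Let d be the share of an arm that is filled in. Let g be the mean change those patients would have made between their last observed score and T3. Then

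LOCF effect = true effect - d(exercise) × g(exercise) + d(control) × g(control).

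If d and g are the same in both arms, the two terms cancel and there is no bias. Otherwise bias generally remains.

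**3. Assumed inputs (not in the protocol).** The control mean rises in equal steps from 40 at T0 to 56.3 at T3. The effect builds in equal steps from 0 to 12.3. SD is 17.6 at each visit, with 41 per arm. The last visit of a lost patient is T0, T1 or T2 with equal chance, at random within arm.

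- Control: g = (16.3 + 10.9 + 5.4) / 3 = 10.9.
- Unobserved benefit: (12.3 + 8.2 + 4.1) / 3 = 8.2.
- Exercise: g = 10.9 + 8.2 = 19.1.

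**4. Results for the estimate.**

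| Loss, control / exercise | True effect | Calculation | LOCF estimate |
|---|---|---|---|
| 20% / 20% | 12.3 | 12.3 - 0.2 × 8.2 | 10.7 |
| 10% / 30% | 12.3 | 12.3 - 0.3 × 19.1 + 0.1 × 10.9 | 7.7 |
| 30% / 10% | 12.3 | 12.3 - 0.1 × 19.1 + 0.3 × 10.9 | 13.7 |
| 10% / 30% | 0 | -0.2 × 10.9 | -2.2 |
| 30% / 10% | 0 | +0.2 × 10.9 | +2.2 |
| 20% / 20% | 0 | terms cancel | 0 |

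**5. Power and type I error.** Mixing early and late scores also widens the spread. The variance in an arm is 17.6² + d × mean(g²) - (d × mean g)².

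- With 20% loss in both arms the variances are 332.6 (control) and 380.0 (exercise). The standard error is √[(332.6 + 380.0) / 41] = 4.17. Since 10.66 / 4.17 = 2.56, power is about 72%.
- With 10% / 30% loss and a true 12.3, the variances are 322.4 and 404.3 and the standard error is 4.21. Since 7.67 / 4.21 = 1.82, power is about 44%.
- With 10% / 30% loss and no true effect, the variances are 322.4 and 340.5 and the standard error is 4.02. Since 2.17 / 4.02 = 0.54, the two-sided rejection rate is about 8.4%.

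Simulation with a correlation of 0.5 between adjacent visits agrees: 71-72%, 44% and 8-9%. With equal loss and no effect, it gives about 5%.

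**6. Dependence on the assumed recovery.**

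- No control recovery (flat at 56.3) and 20% loss in both arms: still 12.3 - 0.2 × 8.2 = 10.7, power about 76%.
- Smaller recovery (50 to 56.3) and 10% / 30% loss: g is 4.2 in control and 12.4 in exercise, so 12.3 - 0.3 × 12.4 + 0.1 × 4.2 = 9.0, power about 61%.
- All of the benefit after the last observed visit and 20% loss in both arms: 12.3 - 0.2 × 12.3 = 9.84.
- An equal unobserved recovery of 20 points in both arms: 12.3 - 0.2 × 20 = 8.3 if exercise loses 30% and control 10%, and 12.3 + 0.2 × 20 = 16.3 the other way round.

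**The case against.** The best defence is that LOCF does little harm in the case the protocol plans for. At 20% loss, balanced between arms, the illustrated estimate falls by 1.6 points towards no effect. With equal dropout and no true effect, the type I error is kept. Inflation needs unequal dropout, and nothing in the protocol sizes that. The trajectory, the last-visit pattern and the 10% / 30% split are all assumed. This stands, and it limits what can be claimed.

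A reader might infer several stronger points that the protocol does not support:

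- **LOCF is biased under any dropout and always inflates type I error.** It is not: step 2 of the working shows the case in which the bias vanishes.
- **The plan expects high attrition or steep change in QoL.** Limitations says only that attrition may be high, and no QoL trajectory is given. The Intervention section supports improvement, not its steepness.
- **The plan carries QoL past death.** Statistical analysis does not mention death. Background names the leading cause of death after transplant, not how often it occurs by day 100. Carrying scores past death is a possible consequence of the rule, not a stated one.
- **Day 100 is the primary time point.** The protocol does not name one. The point concerns the T3 contrast.

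It might also be said that missing-data detail belongs in an analysis plan that is not shown. That does not answer the point, because the protocol has already fixed the method, and an analysis plan that follows it would use LOCF.

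**Conclusion.** The point holds in a conditional form. The protocol fixes a single missing-data method whose no-change assumption conflicts with its own description of recovery. Followed as written, that method can give a wrong T3 difference.

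Bias arises if the benefit builds after the last observed visit, whatever the balance of dropout, or if dropout differs by arm while patients are still recovering. Under the assumptions in the working, a true 12.3 becomes 10.7 with equal 20% loss, and 7.7 or 13.7 with a 20-point difference in loss. With no true effect and that same difference, the bias is about 2.2 points in either direction and the type I error 8-9%. The direction follows from the formula. The sizes are illustrations, because the protocol gives neither dropout by arm nor a QoL course.

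The change should be made before analysis, since it governs the primary outcome and needs no more patients.

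**What to change.** **Change.**

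- Delete LOCF from Statistical analysis. Analyse the T1 to T3 QoL scores of all randomised patients with a likelihood-based mixed model for repeated measures (group by visit, T0 score as covariate), and report the group difference at T3. SPSS, already the planned software, does this with MIXED.
- Add one missing-not-at-random sensitivity analysis, for example delta-adjusted multiple imputation.
- State that QoL is not imputed after death, and report any deaths by arm.
- Reconcile the T0 assessment. Primary and secondary outcomes says that all outcomes are measured at T0, but Table 1 under Participant timeline marks no QLQ-C30 at t0. The T0 covariate relies on the former. If Table 1 were right, a patient lost before T1 would have no score to carry forward under LOCF either.

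Ranking death as the worst outcome, or scoring an uncompleted sit-to-stand test as worst, are optional extras and not needed to resolve this point.

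**Cost.** The change needs modest programming and an amendment, which requires ethics re-approval under Protocol amendments. The mixed model assumes that data are missing at random. It does not by itself deal with patients who leave because they are doing badly, which is why the sensitivity analysis is needed. A patient with no score after T0 adds nothing to the model, so the number of such patients should be reported by arm.
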